# INTRODUCTION

Neck pain represents a major health problem, with a high socio-economic impact^1^. Among the working population, its annual prevalence varies between 30 and 50%^2^, increasing significantly in fighter pilots^3^. According to NATO, flight-related neck pain was estimated to cost up to 7 man-years of lost productivity in fighter pilots, drastically reducing the return on investment in pilot training, estimated at more than 2 million euros^4^. Its multifactorial etiology has contributed to the consideration of certain occupational exposures (physical and psychosocial) as causal factors related to absenteeism from work^5,6^ in the general population, and to flight safety in the face of physical demands by G-forces in fighter pilots^3–5^.

Flight-related neck pain has been defined as a clinical entity specific to military pilots^4^. It refers to the significant neck pain that occurs during or within 48 hours after the flight. It does not refer to pain that is obviously due to other activities or causes. Previous studies have identified mobility limitations in the cervical region, force limitations and cervical impairment in fighter pilots who suffer from flight-related neck pain^3,7,8^. Over the last decade, investment in technological development by national defense administrations has transformed military aviation and, consequently, the training of fighter pilots. However, strategies aimed at reducing the direct and indirect costs arising from work-related musculoskeletal disorders in fighter pilots are limited and not very clarifying^4^.

Current evidence-based guidelines for the management of neck pain highlight the importance of multimodal physiotherapy programs based on the interaction between techniques such as soft tissues mobilization, exercise and electrical stimulation^4,9,10^. The benefits of combining both interventions lie in the possible effects on the impairments of flexibility of key muscles related to the lower cervical and upper thoracic spine^4,10^ The combination of interferential current with other therapeutic modalities has been investigated on neck pain (plus supervised exercise)^9^, low back pain (plus manual therapy)^11,12^ or shoulder pain (simultaneously interferential current plus manual therapy)^13^. Nevertheless, the results are still uncertain^14^. Recently, NATO has recommended electrical stimulation as first-choice treatment in fighter pilots who suffer from flight-related neck pain^4^. However, it is unknown what effect may electrical stimulation add in conjunction with simultaneous application of manual therapy (electro-massage) in the neck region of fighter pilots.

The clinical efficacy of the cervical coordination exercises versus protocols that only include strength or endurance in reducing pain has also been analysed^15^. In recent years, the development of rehabilitation technologies has reported differences between types of exercise according to whether the exercise requires the individual to focus on their body while moving a body region (exercise with an internal locus of movement control) or to focus on clues provided by the environment, with the effect being achieved after movement has been performed (exercise with an external locus). Previous studies about neck pain have reported improvements in motor skill learning when the type of exercise was guided by means of an external locus located in the head (eg. Laser pointer)^16^. The clinical utility has been explained as facilitating the establishment of effective neural connections that optimize exercise performance^17^.

Notwithstanding, there is no clear consensus on which is the most effective approach for fighter pilots with flight-related neck pain.

The aim of this study will be to analyse the immediate effects of a 4-week multimodal physiotherapy program which combines cervical supervised exercises with laser-guided feedback (ELGF) and interferential current electro massage (ICE) in fighter pilots with flight-related neck pain.

# OBJECTIVES

## General objectives

1. To assess cervical status and design a reliable assessment protocol based on the biopsychosocial model in military pilots with flight-related neck pain.

2. To analyse the relationship between cognitive demand and stress in each flight segment using Heart Rate Variability (HRV) in a flight simulator.

3. To develop and analyse the impact of a multimodal physiotherapy programme on clinimetric and psychophysiological variables in fighter pilots with flight-related neck pain.

## Specific objectives

1. To assess the degree of disability, limitation of cervical mobility, perceived pain, cervical repositioning and electromyographic disturbances and degree of kinesiophobia and catastrophism in fighter pilots with flight-related neck pain.

2. To find out the possible associations according to age and flight experience with the clinimetric variables assessed.

3. To analyse the VFC in the take-off, flight and landing segments during emergency manoeuvres in the flight simulator.

4. To determine what changes occur during flight and which segment produces the greatest stress response in pilots.

5. Design and implement a multimodal physiotherapy programme combining supervised cervical exercise with laser-guided feedback (ELGF) and interferential current electro-massage (ICE).

6. To analyse the impact of the multimodal physiotherapy programme on variables analysed in the designed assessment protocol and on physiological changes using HRV.

# METHODS

## Study design

We propose to conduct a single-blind randomised clinical trial with concealed allocation, intention-to-treat analysis and in which the treatment allocation is not known to the evaluator and the statistical investigator. The study will be conducted in accordance with the recommendations of the CONSORT^18^. statements. The future study will be conducted in accordance with the Declaration of Helsinki.

All data will be collected in the same room, at a temperature of 22–25 °C. Always in the same order and under the same environmental conditions for all subjects, both before and after the intervention.

## Participants

Convenience sampling will be followed. The inclusion criteria will be: (i) fighter pilots (male and female) who, at the time of the assessment, are an instructor or student attached to the 23rd Wing of the Talavera Air Base, Air Force (FAE), Badajoz; (ii) fighter pilots diagnosed with flight-related neck pain according to the International Classification proposed by a NATO expert panel4; (iii) fighter pilots diagnosed with flight-related neck pain according to the International Classification proposed by a NATO expert panel; (iv) fighter pilots diagnosed with flight-related neck pain according to the International Classification proposed by a NATO expert panel5; a minimum perceived pain score of 3/10 on the Numerical Pain Rating Scale (NPRS) on the early morning assessment within 48 hours of the last flight; (iv) scores of ≥5 points on the Neck Disability Index (NDI), and a cervical positioning error of ≥4.5°^19^. Exclusion criteria shall be: (i) Personal Psychological Apprehension Scale (PPAS) score greater than 37.5^20^; (ii) contraindication to electrical stimulation; (iii) having received physiotherapy or any other routine medical care six weeks prior to data collection; (iv) any regular use of medications known to affect autonomic nervous system (ANS) function or pain perception, including opioids, antidepressants, benzodiazepines, anti-inflammatory drugs and beta-blockers, two weeks prior to participation in this study; and (v) being involved in ongoing medico-legal disputes.

- - 1. Numeric Pain Rating Scale

Numeric Pain Rating Scale (NPRS) is a 11-point numeric rating scale, where 0 denotes “no pain” and 10 denotes “the maximum bearable pain”. The minimum clinically important difference (MCID) for this tool have been established at 1.3 points and the minimum detectable change (MDC) at 2.1 points^9^, in individuals with neck pain. The NPRS is a valid scale with moderate test-retest reliability in this population (ICC: 0.76, 95% CI 0.51 to 0.87)^9,21^.

## Outcome measures

### Neck Disability Index

Cervical Disability will be evaluated using the validated Spanish version of the Neck Disability Index (NDI)^22^. [This](https://www.collinsdictionary.com/es/diccionario/ingles-espanol/this) [questionnaire](https://www.collinsdictionary.com/es/diccionario/ingles-espanol/questionnaire) [consists](https://www.collinsdictionary.com/es/diccionario/ingles-espanol/consist) [of](https://www.collinsdictionary.com/es/diccionario/ingles-espanol/of) 10 [sections](https://www.collinsdictionary.com/es/diccionario/ingles-espanol/section), 4 [of](https://www.collinsdictionary.com/es/diccionario/ingles-espanol/of) [them](https://www.collinsdictionary.com/es/diccionario/ingles-espanol/them) [are](https://www.collinsdictionary.com/es/diccionario/ingles-espanol/are) [related](https://www.collinsdictionary.com/es/diccionario/ingles-espanol/related_2) [to](https://www.collinsdictionary.com/es/diccionario/ingles-espanol/to) [subjective](https://www.collinsdictionary.com/es/diccionario/ingles-espanol/subjective) [symptoms](https://www.collinsdictionary.com/es/diccionario/ingles-espanol/symptom) (pain [intensity](https://www.collinsdictionary.com/es/diccionario/ingles-espanol/intensity), [headache](https://www.collinsdictionary.com/es/diccionario/ingles-espanol/headache), [ability](https://www.collinsdictionary.com/es/diccionario/ingles-espanol/ability) [to](https://www.collinsdictionary.com/es/diccionario/ingles-espanol/to) [concentrate](https://www.collinsdictionary.com/es/diccionario/ingles-espanol/concentrate) [and](https://www.collinsdictionary.com/es/diccionario/ingles-espanol/and) [sleep](https://www.collinsdictionary.com/es/diccionario/ingles-espanol/sleep) quality) [and](https://www.collinsdictionary.com/es/diccionario/ingles-espanol/and) [the](https://www.collinsdictionary.com/es/diccionario/ingles-espanol/the) [other](https://www.collinsdictionary.com/es/diccionario/ingles-espanol/other) 6 [are](https://www.collinsdictionary.com/es/diccionario/ingles-espanol/are) [related](https://www.collinsdictionary.com/es/diccionario/ingles-espanol/related_2) [to](https://www.collinsdictionary.com/es/diccionario/ingles-espanol/to) [basic](https://www.collinsdictionary.com/es/diccionario/ingles-espanol/basic) [activities](https://www.collinsdictionary.com/es/diccionario/ingles-espanol/activity) [of](https://www.collinsdictionary.com/es/diccionario/ingles-espanol/of) [daily](https://www.collinsdictionary.com/es/diccionario/ingles-espanol/daily) [life](https://www.collinsdictionary.com/es/diccionario/ingles-espanol/life) (personal [care](https://www.collinsdictionary.com/es/diccionario/ingles-espanol/care), [ability](https://www.collinsdictionary.com/es/diccionario/ingles-espanol/ability) [to](https://www.collinsdictionary.com/es/diccionario/ingles-espanol/to) [lift](https://www.collinsdictionary.com/es/diccionario/ingles-espanol/lift) [weights](https://www.collinsdictionary.com/es/diccionario/ingles-espanol/weight), [reading](https://www.collinsdictionary.com/es/diccionario/ingles-espanol/reading), [work](https://www.collinsdictionary.com/es/diccionario/ingles-espanol/work), [driving](https://www.collinsdictionary.com/es/diccionario/ingles-espanol/driving), [leisure](https://www.collinsdictionary.com/es/diccionario/ingles-espanol/leisure) [activities](https://www.collinsdictionary.com/es/diccionario/ingles-espanol/activity) [and](https://www.collinsdictionary.com/es/diccionario/ingles-espanol/and) [leisure](https://www.collinsdictionary.com/es/diccionario/ingles-espanol/leisure) time). NDI has been shown to be valid and reliable for measuring pain and cervical disability (Cronbach Alpha: 0,944; ICC: 0.88, 95% CI 0.80 to 0.93)^21,23^. It is he most used scale for neck pain and disability, having been previously used [in](https://www.collinsdictionary.com/es/diccionario/ingles-espanol/in_1) fighter pilots^8^. The MCID has been reported in 7 points^21^ and MDC at 9.8 points^9^.

Each item of this self-completed questionnaire presents six possible answers. Scores range from 0 (no disability) to 5 (complete disability) points. The total score (maximum 50 points) is calculated by adding up the responses for each item. [The](https://www.collinsdictionary.com/es/diccionario/ingles-espanol/the) [interpretation](https://www.collinsdictionary.com/es/diccionario/ingles-espanol/interpretation) [of](https://www.collinsdictionary.com/es/diccionario/ingles-espanol/of) [the](https://www.collinsdictionary.com/es/diccionario/ingles-espanol/the) [questionnaire](https://www.collinsdictionary.com/es/diccionario/ingles-espanol/questionnaire) is classified as follows: "no disability" (NDI < 10% of maximum total score), "mild" (NDI between 10% and < 30%), "moderate" (NDI between 30% and < 50%), "severe" (NDI between 50% and < 70%) or "very severe" (NDI >= 70%) degree of disability.

### Catastrophizing Pain

Catastrophizing is a cognitive factor that involves an exaggerated negative appraisal toward pain stimuli and pain experience^24^. Pain Catastrophizing Scale (PCS) [is](https://www.collinsdictionary.com/es/diccionario/ingles-espanol/is_1) [a](https://www.collinsdictionary.com/es/diccionario/ingles-espanol/a_1) [self](https://www.collinsdictionary.com/es/diccionario/ingles-espanol/self_1)-[administered](https://www.collinsdictionary.com/es/diccionario/ingles-espanol/administered) [scale](https://www.collinsdictionary.com/es/diccionario/ingles-espanol/scale) (Likert scale) [of](https://www.collinsdictionary.com/es/diccionario/ingles-espanol/of) 13 [items](https://www.collinsdictionary.com/es/diccionario/ingles-espanol/item) [and](https://www.collinsdictionary.com/es/diccionario/ingles-espanol/and) [one](https://www.collinsdictionary.com/es/diccionario/ingles-espanol/one_1) [of](https://www.collinsdictionary.com/es/diccionario/ingles-espanol/of) [the](https://www.collinsdictionary.com/es/diccionario/ingles-espanol/the) [most](https://www.collinsdictionary.com/es/diccionario/ingles-espanol/most_2) [used](https://www.collinsdictionary.com/es/diccionario/ingles-espanol/used) and reliable (Cronbach [alpha](https://www.collinsdictionary.com/es/diccionario/ingles-espanol/alpha): 0.79)^25^ [to](https://www.collinsdictionary.com/es/diccionario/ingles-espanol/to) [assess](https://www.collinsdictionary.com/es/diccionario/ingles-espanol/assess) [the](https://www.collinsdictionary.com/es/diccionario/ingles-espanol/the) catastrophizing [of](https://www.collinsdictionary.com/es/diccionario/ingles-espanol/of) [pain](https://www.collinsdictionary.com/es/diccionario/ingles-espanol/pain). [In](https://www.collinsdictionary.com/es/diccionario/ingles-espanol/in_1) [it](https://www.collinsdictionary.com/es/diccionario/ingles-espanol/it), [subjects](https://www.collinsdictionary.com/es/diccionario/ingles-espanol/subject) [refer](https://www.collinsdictionary.com/es/diccionario/ingles-espanol/refer) [to](https://www.collinsdictionary.com/es/diccionario/ingles-espanol/to) [their](https://www.collinsdictionary.com/es/diccionario/ingles-espanol/their) [past](https://www.collinsdictionary.com/es/diccionario/ingles-espanol/past) [painful](https://www.collinsdictionary.com/es/diccionario/ingles-espanol/painful) [experiences](https://www.collinsdictionary.com/es/diccionario/ingles-espanol/experience) [and](https://www.collinsdictionary.com/es/diccionario/ingles-espanol/and) [indicate](https://www.collinsdictionary.com/es/diccionario/ingles-espanol/indicate) [the](https://www.collinsdictionary.com/es/diccionario/ingles-espanol/the) [degree](https://www.collinsdictionary.com/es/diccionario/ingles-espanol/degree) [to](https://www.collinsdictionary.com/es/diccionario/ingles-espanol/to) [which](https://www.collinsdictionary.com/es/diccionario/ingles-espanol/which) [they](https://www.collinsdictionary.com/es/diccionario/ingles-espanol/they) [experienced](https://www.collinsdictionary.com/es/diccionario/ingles-espanol/experienced) [each](https://www.collinsdictionary.com/es/diccionario/ingles-espanol/each) [of](https://www.collinsdictionary.com/es/diccionario/ingles-espanol/of) [the](https://www.collinsdictionary.com/es/diccionario/ingles-espanol/the) 13 [thoughts](https://www.collinsdictionary.com/es/diccionario/ingles-espanol/thought) [or](https://www.collinsdictionary.com/es/diccionario/ingles-espanol/or) [feelings](https://www.collinsdictionary.com/es/diccionario/ingles-espanol/feeling). [The](https://www.collinsdictionary.com/es/diccionario/ingles-espanol/the) [score](https://www.collinsdictionary.com/es/diccionario/ingles-espanol/score) [ranges](https://www.collinsdictionary.com/es/diccionario/ingles-espanol/range_2) [from](https://www.collinsdictionary.com/es/diccionario/ingles-espanol/from) 0 (never) [to](https://www.collinsdictionary.com/es/diccionario/ingles-espanol/to) 4 (always).

Total score [reflects](https://www.collinsdictionary.com/es/diccionario/ingles-espanol/reflect) [the](https://www.collinsdictionary.com/es/diccionario/ingles-espanol/the) [level](https://www.collinsdictionary.com/es/diccionario/ingles-espanol/level) [of](https://www.collinsdictionary.com/es/diccionario/ingles-espanol/of) catastrophism obtained [of](https://www.collinsdictionary.com/es/diccionario/ingles-espanol/of) [the](https://www.collinsdictionary.com/es/diccionario/ingles-espanol/the) subject's [pain](https://www.collinsdictionary.com/es/diccionario/ingles-espanol/pain) is obtained (higher score means worse result).

### Kinesiophobia

[The](https://www.collinsdictionary.com/es/diccionario/ingles-espanol/the) [Spanish](https://www.collinsdictionary.com/es/diccionario/ingles-espanol/spanish) [version](https://www.collinsdictionary.com/es/diccionario/ingles-espanol/version) [of](https://www.collinsdictionary.com/es/diccionario/ingles-espanol/of) [the](https://www.collinsdictionary.com/es/diccionario/ingles-espanol/the) Tampa Kinesiophobia [Scale](https://www.collinsdictionary.com/es/diccionario/ingles-espanol/scale) (TSK-11) [will be](https://www.collinsdictionary.com/es/diccionario/ingles-espanol/was) [used](https://www.collinsdictionary.com/es/diccionario/ingles-espanol/used)^26^. [This](https://www.collinsdictionary.com/es/diccionario/ingles-espanol/this) subjective [questionnaire](https://www.collinsdictionary.com/es/diccionario/ingles-espanol/questionnaire) [contains](https://www.collinsdictionary.com/es/diccionario/ingles-espanol/contain) 11 [items](https://www.collinsdictionary.com/es/diccionario/ingles-espanol/item) [designed](https://www.collinsdictionary.com/es/diccionario/ingles-espanol/design) [to](https://www.collinsdictionary.com/es/diccionario/ingles-espanol/to) [assess](https://www.collinsdictionary.com/es/diccionario/ingles-espanol/assess) [the](https://www.collinsdictionary.com/es/diccionario/ingles-espanol/the) patient's [fear](https://www.collinsdictionary.com/es/diccionario/ingles-espanol/fear) [of](https://www.collinsdictionary.com/es/diccionario/ingles-espanol/of) [moving](https://www.collinsdictionary.com/es/diccionario/ingles-espanol/moving) [and](https://www.collinsdictionary.com/es/diccionario/ingles-espanol/and) [re](https://www.collinsdictionary.com/es/diccionario/ingles-espanol/re_1)-injury. [Score](https://www.collinsdictionary.com/es/diccionario/ingles-espanol/score) [ranges](https://www.collinsdictionary.com/es/diccionario/ingles-espanol/range_2) [from](https://www.collinsdictionary.com/es/diccionario/ingles-espanol/from) 11 [to](https://www.collinsdictionary.com/es/diccionario/ingles-espanol/to) 44 [points](https://www.collinsdictionary.com/es/diccionario/ingles-espanol/point). Each item is associated with a 4-point Likert scale (1= “strongly disagree”,4= “strongly agree”). Higher scores correspond with a greater fear of pain, movement and injury. The Spanish version of the TSK-11 has shown good reliability and validity (Cronbach [alpha](https://www.collinsdictionary.com/es/diccionario/ingles-espanol/alpha): 0.79)^26^. [A](https://www.collinsdictionary.com/es/diccionario/ingles-espanol/a_1) [higher](https://www.collinsdictionary.com/es/diccionario/ingles-espanol/higher) [score](https://www.collinsdictionary.com/es/diccionario/ingles-espanol/score) [indicates](https://www.collinsdictionary.com/es/diccionario/ingles-espanol/indicate) [higher](https://www.collinsdictionary.com/es/diccionario/ingles-espanol/higher) [levels](https://www.collinsdictionary.com/es/diccionario/ingles-espanol/level) [of](https://www.collinsdictionary.com/es/diccionario/ingles-espanol/of) kinesiophobia.

### Myoelectric activity

Myoelectric activity will be measured with surface electromyography (sEMG) according to the recommendations of the NATO expert panel^4^. A protocol similar to that established in previous studies will be used^27,28^. The sEMG recordings will be taken using mDurance® system (mDurance Solutions SL, Granada, Spain). It is a portable and low-costs EMG system, which has proved to be a valid tool to measure muscle activity during dynamic contractions^29^. The system consists of a Shimmer3 EMG unit (Realtime Technologies Ltd, Dublin, Ireland), a bipolar sEMG sensor for the acquisition of superficial muscle activity. Each Shimmer sensor is composed of two sEMG channels, which register the electrical signal via bluetooth with a sampling rate at 1,024 Hz. Shimmer applies a bandwidth 8.4 kHz the EMG signal resolution is 24 bits and overall amplification of 100–10,000 V/V.

As sEMG recommended for the noninvasive assessment of muscles SENIAM^30^, the electrodes placement areas will be shaved if necessary, and disinfected with 70% alcohol. Next, five disposable, bipolar, self-adhesive electrodes with pre-gelled surface discs and an active diameter with dimensions 41 mm × 21 mm, diameter 10 mm (Ag/AgCl, Blue Sensor N-00-S, Medicotest A/S, Olstykke, Denmark) will be placed pairwise (with an interelectrode distance of 21 ± 1 mm), on the muscle belly parallel to the muscle fibers. Myoelectric activity will be recorded from two muscles bilaterally: the anterior neck (the lower part of the sternocleidomastoid muscle belly), and the upper shoulders (upper trapezius muscle bellies, midway between the occiput and the acromion).

A reference electrode will be placed around the bone rim of the acromion.

Firstly, participants will be instructed through pre-registration tests before myoelectric activity recordings will be made. Pre-recording tests consisted of the subject pushing their heads against manual resistance in extension, as indicated by Pousette et al^27^. Subjects will be comfortably seated in the gondola’s flight seat, with their back against the seat and their trunk and shoulders fixed to a rigid seat back using two straps placed along both shoulders, and the elbows with a flexion of 60º approximately. The participants will be placed in a neutral cranio-cervical position when they will be instructed to push with increasing force up to maximal voluntary force and hold for 3 seconds in order to avoid injury and minimize the risk of dynamic contractions. Three trials will be done, with 1 minute rest in between each other, in order to enhance maximum voluntary contraction (MVC) stability^27^.

Then, three trials (with a duration of 1 second each attempt) to 15-30% MVC will be performed, [as](https://www.collinsdictionary.com/es/diccionario/ingles-espanol/as) [proposed](https://www.collinsdictionary.com/es/diccionario/ingles-espanol/proposed) [by](https://www.collinsdictionary.com/es/diccionario/ingles-espanol/by) Calamita [et](https://www.collinsdictionary.com/es/diccionario/ingles-espanol/et) [al](https://www.collinsdictionary.com/es/diccionario/ingles-espanol/al)^31^, and the mean of the two highest trials will be defined as MVC.

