## Sample size

G*power 3.1 software will be used to calculate the sample size required to detect changes in the primary outcome (NPRS scale and JPSE). The calculations will be based on the detection differences of 2.5 points in the NPRS (MCID (minimal clinically important difference) (estimated for a variance in patients with neck pain of 10 points)^40^, assuming a standard deviation (SD) of 2.5 points.

Assuming an effect size (F-test) of 0.27 for ANOVA: repeated measures, within-between interaction groups differences, an alpha level of .05, and power of 80%, a total sample size of 30 participants will be estimated. The sample will be inflated by 10% to account for potential dropouts, resulting in a final target sample size of 34. This calculation showed that a sample size of 17 participants per group will be needed for a confidence interval of 95%, with a power of 80%, assuming a bilateral significance of .05.

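### The only sentence that defines MVC ties it to the 15–30% MVC trials, so read literally the value labelled maximal is submaximal

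*Protocol*

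**What the plan says.** The Myoelectric activity section of the protocol sets out two series of contractions.

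- **First series.** Seated pilots "push with increasing force up to maximal voluntary force and hold for 3 seconds". The series is repeated: "Three trials will be done, with 1 minute rest in between each other, in order to enhance maximum voluntary contraction (MVC) stability". It is introduced as preparatory: "participants will be instructed through pre-registration tests before myoelectric activity recordings will be made". No rule turns these pushes into a number.
- **Second series.** After the maximal pushes, "three trials (with a duration of 1 second each attempt) to 15-30% MVC will be performed". The same sentence closes with the only definition of MVC in the protocol: "the mean of the two highest trials will be defined as MVC".

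The section names no sEMG summary variable and does not say whether amplitudes are divided by MVC. Electromyographic findings fall under specific objective 1, and the programme's effect on the assessed variables falls under specific objective 6. The Sample size section names the NPRS and JPSE as primary.

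**The concern.** The definition sits in the sentence about the 15–30% trials, so the nearest trials that it can refer to are those. An assessor who follows the sentence would take the two highest submaximal pushes, average them and record the result as the maximum. That conflicts with the rest of the section in two ways. The target of the second series is a fraction of MVC, so MVC cannot sensibly be the outcome of that series. And the maximal series, done for the sake of a stable MVC, would contribute nothing to it.

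At stake is the meaning of any sEMG result that uses MVC. If MVC is a denominator, the scale is wrong and the denominator can drift between visits, because the target is a band and not a point. If MVC is itself reported, a submaximal quantity carries a maximal label. This is a rule for collecting data: a later analysis plan cannot restore a maximal reference if the maximal pushes were treated as practice and not kept.

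**Working it through.** The protocol states no figure for this point, so there is none to reproduce. The sample size statement ("a total sample size of 30 participants will be estimated") does not depend on it. The check is a reading of the section followed by simple arithmetic.

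**Step 1. The two series side by side**

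| | First series | Second series |
|---|---|---|
| Effort | maximal | 15–30% MVC |
| Trials | 3 | 3 |
| Duration | 3 seconds | 1 second |
| Described as | preparatory to the recordings | performed next |
| Value derived in the same sentence | none | MVC, from the two highest trials |

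**Step 2. Consistency.** If the maximal series supplies the MVC, the 15–30% target can be set and the section is coherent. If the second series supplies it, two quantities share one name: the maximum used to set the target, and the later mean of submaximal trials. The text as it stands gives the second result.

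**Step 3. Size of the literal reference.** Set the true maximum to 1. Each second-series trial then lies between 0.15 and 0.30, and so does the mean of the two highest:

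- lower bound: (0.15 + 0.15)/2 = 0.15
- upper bound: (0.30 + 0.30)/2 = 0.30

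**Step 4. Effect on a normalised value.** This step needs two assumptions that the protocol does not state: that sEMG is divided by this MVC, and that amplitude is roughly proportional to force. The inflation factor is 1/reference:

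| Reference as share of true maximum | Inflation of %MVC |
|---|---|
| 0.30 | 1/0.30 = 3.33 |
| 0.25 | 1/0.25 = 4.00 |
| 0.20 | 1/0.20 = 5.00 |
| 0.15 | 1/0.15 = 6.67 |

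**Step 5. Movement of the reference between visits.** Under the same assumptions, the extreme case is one end of the band at baseline and the other after treatment: 0.30/0.15 = 2. A smaller shift, from 0.20 to 0.25, gives 0.25/0.20 = 1.25. An inflation factor that stays constant cancels in a relative pre-post change. A reference that moves does not.

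**Step 6. After correction.** With MVC taken from the maximal series, the reference is about 1 and the inflation factor about 1.

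**The case against.** The strongest reply is that this is a badly placed clause and no more. The maximal pushes come first, their stated purpose concerns MVC, and a word like highest fits a maximal series best. The authors probably meant the two highest of those three. That is plausible, and if so both the submaximality and the inconsistency disappear. But the sentence does not say it, no other section does, and the maximal pushes are presented as preparation for the recordings. The wording still needs correcting.

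The other side is right to limit the following stronger readings.

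- **A reader might infer that all sEMG results will be inflated.** The protocol never says that sEMG is normalised to MVC. The 3.3- to 6.7-fold figures are conditional on that, and on proportionality of amplitude to force.
- **A reader might infer that the definition is strictly circular.** The earlier maximal pushes could set the 15–30% target in practice. The rule is therefore inconsistent, with two meanings for one term, but it can be carried out.
- **A reader might infer that a drifting reference would produce a false treatment effect.** The trial is randomised, the evaluator is blinded to allocation, and the analysis tests the group-by-time interaction. Variation in effort unrelated to arm adds noise to both groups. The experimental group does train cervical motor control, so a difference in how the push is performed is conceivable, but nothing in the protocol shows one.
- **A reader might infer that the protocol should fix one exact percentage.** The section describes manual resistance and names no force gauge or feedback display, so holding a single value might need equipment that is not described.

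The procedure is also attributed to cited studies that were not available, so their intent cannot settle the matter.

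**Conclusion.** The point stands as an error in the stated rule. Read literally, MVC is defined from trials at 15–30% of maximum, which contradicts both its name and its use as the base for that target. The maximal trials yield no value.

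The numerical consequence is conditional. If sEMG is expressed relative to this MVC and amplitude is roughly proportional to force, %MVC values are about 3.3 to 6.7 times too large, and the reference can vary up to two-fold in the extreme case. That variation would mainly reduce precision in the pre-post comparison; the documents do not support calling it a spurious treatment effect. If MVC is itself the outcome, the same wording means that it is not a maximal measure.

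The reach is limited to a non-primary outcome under specific objectives 1 and 6. The primary outcomes and the sample size are untouched. It should be corrected because the cost is small and because data collected under the wrong reading may not be recoverable.

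**What to change.** Amend the Myoelectric activity section in three respects:

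1. Define MVC as the mean of the two highest of the three maximal 3-second trials, and move that definition to the text on those trials.
2. State that the maximal trials are recorded and kept at both baseline and post-treatment visits.
3. Say in a separate sentence what the 15–30% MVC trials are used for.

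If sEMG amplitudes are to be expressed relative to MVC, the protocol or the analysis plan should say so. The cost is a short change of wording. The maximal trials are already part of the procedure, so no contraction is added; the only practical demand is that their signals are stored.
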